Facilities and Senior High Rises that are involved in providing services to the residents. They could be activity directors, social workers, outreach coordinators, care coordinators, etc. These individuals are not specifically trained to deliver exercise interventions as part of their job. We will work with our community stakeholders and the building managers to identify staff activity personnel at each of the sites who would be involved in this research study. All exercise leaders and identified staff activity personnel will be trained in the delivery of the exercise program prior to leading any exercises classes. The staff activity personnel will participate in a one hour training sessions in which the rationale and the general format of the program will be explained. During these training sessions the activity staff personnel will participate in a sample exercise class. In addition to the 2 training sessions, the activity staff personnel will be able to observe the 12 week exercise session delivered by the exercise leader at their facility. They will be given the opportunity to observe all 24 sessions if they would like. In addition to training the exercise leaders and activity staff personnel, we will provide printed materials explaining the exercise program that we developed in our pilot work (see appendix). After training, the exercise leader will determine if the staff activity personnel is ready to lead the exercise class. The exercise leader will consider the following when determining if the individual is ready to lead the class: 1) attendance at training sessions, 2) attendance at exercise sessions, 3) interactions with research participants, and 4) understanding of the exercise program including all safety considerations. A study investigator ([name] or [name] or one of the exercise leaders) will meet with the staff activity personnel or email them periodically (i.e. during weeks 1, 3, 6, and 10 of the 12 week exercise program) to observe the intervention, monitor treatment fidelity, and to answer any questions. If the study team believes the staff activity person is not ready to lead a class safely and per protocol at a particular site, their class will also be led by an exercise leader.

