## **4 SELECTION AND ENROLLMENT OF PARTICIPANTS**

We will recruit participants from the UPMC Independent Living Facilities (ILFs), other Independent Living Facilities, Senior Housing sites, and Community Centers. Within UPMC there are eight different ILFs with over 700 residents. UPMC is affiliated with 32 different Senior Housing sites that house over 2,000 residents. We anticipate enrolling subjects from 10 ILFs and from approximately 24 of the Senior Housing sites for a total of approximately 34 sites. However, the number of participants per site will vary and we will continue adding sites and enrolling participants until the planned sample size is met for the primary Aim (i.e. n=280).

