## **5 STUDY INTERVENTIONS**

### **5.1 Overview**

The exercise interventions will be delivered in 2 phases. The first phase or 12 week class will be delivered by the exercise leader. The second phase or 12 week class will begin once the first phase is completed and will be delivered by staff activity personnel. Participants who are randomized to the second phase class (i.e. delivered by staff activity personnel) will repeat the baseline testing prior starting the exercise class.

The facilities will be randomized (described above) to receive either the "On the Move" or a standard group exercise program. Both exercise programs (On the Move and standard) will be group-based and led by a person. Both programs will be delivered by trained exercise leaders or trained staff activity personnel (sustainability component). The frequency and duration of the programs are identical (50 minutes, 2 times a week for 12 weeks). From our past research we have determined that a frequency of 2 times per week for 12 weeks is acceptable to the older adult participants and is an adequate dose to obtain meaningful outcomes.(23) The main difference between the standard and the On the Move group exercise programs is the program content which is described below.

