### **8.2 Intervention Discontinuation**

At any time, the study team may recommend discontinuation of any component of the intervention or intervention group of the study for any of the following reasons:

1. Compelling evidence from this or any other study of an adverse effect of the study intervention(s) that is sufficient to override the potential benefit of the interventions to the target population
2. Compelling evidence from this or any other study of a significant beneficial effect of the study intervention(s), such that it is continued denial to other study group(s) would be unethical
3. A very low probability of addressing the study goals within a feasible timeframe.

The research team may decide at any time to remove a participant from the research study if the team feels the participant is unsafe to continue. Participation in the research study will be discontinued if a participant's walking ability worsens; for example, if a subject who has osteoarthritis of the knees exhibits a significant increase in pain that negatively affects their walking ability. Participants can be removed from the study if they have unstable vital signs as a response to exercise. A participant can also be removed from the study if any new medical condition, injury or illness is discovered during the course of treatment that would make the participant unsafe to continue.

The research team may decide at any time to discontinue training of a staff activity person if the teams feels the staff activity person is unsafe to continue. If training of a staff activity person is discontinued, an exercise leader will take over as instructor for the exercise class to keep our obligation of the exercise class to the community. If such a change becomes necessary after the class has begun, we will exclude that particular class from all analyses. If such a change becomes apparent before the class begins, and the entire class is taught by an exercise leader, we will include the class in Aim 1 analysis.

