## 9 STATISTICAL CONSIDERATIONS

### 9.1 General Design Issues

A randomized trial is needed to control for confounding factors that affect the outcome. There are no ethical issues regarding a randomized trial since both groups will be receiving an active exercise intervention delivered by trained personnel. We carefully considered the advantages and disadvantages of randomizing at the level of the facility and the resident. Given the amount of interaction that occurs between subjects within a facility, it is imperative that we conduct a cluster randomized trial, and randomize by facility to exercise programs. If we randomize at the resident, participants would discuss details of their intervention and cause cross-contamination between the intervention arms. Unlike a traditional trial in which participants are randomized as they are being recruited, a cluster randomized trial also affords the additional benefit of examining the facility characteristics such as type (independent living/senior high rise) and size, and ensuring a balance in those characteristics is achieved by design rather than chance. Once the facilities are randomized to exercise program, we will then randomize within facility for delivery mode (i.e. subjects will be randomized to either an exercise leader or staff activity person led exercise program). Randomization for delivery mode will occur after baseline testing. We will use a commercially available high quality pseudo-random deviate generator such as that available in SAS® (SAS Institute, Inc., Cary, North Carolina) known to be free of serial correlations(56) to randomize facilities to the two arms in a 1:1 ratio, stratified by facility type. In addition, the proposed design reaps the advantages of a paired comparison for the exploratory hypothesis (Aim 2) as both exercise leaders and staff activity personnel will be delivering On the Move in the same set of facilities, where feasible to train a staff person ready to lead the class safely and per protocol.

The main outcomes are self-reported function and disability (Late Life Function and Disability Index/LLFDI) and walking ability (6-minute walk test/6MWT and gait speed). We will also examine satisfaction, attendance rates and adverse event (falls, soft tissue injuries, muscle soreness, etc) rates.

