### 9.3 Data Analyses

#### 9.3.1 Overview

All statistical analyses will be performed or overseen by [name] using SAS® version 9 (SAS Institute, Inc., Cary, North Carolina) and Salford Predictive Miner® (Salford Systems, Inc., San Diego, California) based on the **intention-to-treat** philosophy. We will begin by summarizing data by arm and time point as well as pre- to post-intervention change using appropriate descriptive statistics for continuous (mean, standard deviation, median, range) and categorical (frequencies, percentages) to elicit information about general data quality and their distributional characteristics. Next, we will perform the modeling and inferential analyses to address the main hypotheses. First, the baseline participant characteristics will be compared between the two arms (see Avoidance of Bias below). Although no significant differences are expected, any significant differences will be noted and accounted for as covariates in the main analyses. Second, main analyses to address Aims 1-3 will be performed as outlined below. If residuals reveal violations of linear models assumptions, we will Box-Cox transform(60) the response variables. The two-step protected test approach will be used to control the experimentwise type I error rate from multiple outcomes, and multiple imputation(61, 62) will be used to account for any missing data in the main analysis. Third, we will perform the exploratory analyses to address Aim 4, using a data mining philosophy. Finally, we will perform a set of exploratory analyses to potentially extend our findings and generate new hypotheses, as well as a set of sensitivity analyses to assess the robustness of our findings.

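### Section 8.2 deletes a randomised staff-led class from every analysis if its leader is replaced mid-course, and leaves the Aim 1 baseline undefined for classes that revert before they start

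*Supplement*

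**What the plan says.** All references are to Protocol Version 2.0.

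- **Replacement after the class has begun (8.2).** The team may stop a staff person at any time "if the teams feels the staff activity person is unsafe to continue". An exercise leader then takes over, and: "If such a change becomes necessary after the class has begun, we will exclude that particular class from all analyses".
- **Replacement before the class begins (8.2).** If the need is apparent beforehand and "the entire class is taught by an exercise leader, we will include the class in Aim 1 analysis". Section 3 (Choice of comparators) has a matching readiness rule, for when the study team believes "the staff activity person is not ready to lead a class safely and per protocol at a particular site".
- **Timing.** Section 9.1: "Randomization for delivery mode will occur after baseline testing". Section 5.1: "The second phase or 12 week class will begin once the first phase is completed and will be delivered by staff activity personnel".
- **Analysis principle.** Section 9.3.1 puts all statistical analyses on one footing, "based on the intention-to-treat philosophy". Section 9.3.4 lists an as-treated analysis only as an additional one.
- **Baselines.** Section 6.2.2 gives everyone randomised to the second session, including classes that revert to an exercise leader, a second baseline about 12 weeks after the first. For Aim 2, section 9.3.3 uses the first baseline and repeats the analysis with the second. For Aim 1, section 9.3.2 models change from baseline without saying which baseline a reverted class uses. It also proposes a three-arm sensitivity analysis in which people waiting for staff-led classes act as untreated controls.

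**The concern.** The exclusion is decided after randomisation and for a reason close to an outcome. Aim 3(b) compares adverse-event proportions under staff delivery and between delivery modes, and a class stopped because its leader was thought unsafe is one whose events belong in that comparison. Section 8.2 has no counterpart rule for classes led by an exercise leader, so only one side of the delivery-mode comparison is filtered. If stopped classes do worse, the remaining staff-led results are too favourable, which is the direction of the hypotheses that staff delivery gives comparable gains and similar event rates. The exclusion is not as-treated either: that would reclassify the participants, whereas this rule deletes them.

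The reallocation rule raises a smaller problem, but in the primary aim. Reverted participants enter Aim 1 with two possible starting points, and the choice between them is left open until the data are in hand.

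**Working it through.** **1. Order of events.** Baseline testing comes first, then randomisation to delivery mode (9.1), then the first-phase class, then the second-phase class (5.1). Both a mid-course replacement and a reversion before the start therefore follow randomisation. Nothing in section 9 reconciles the exclusion with 9.3.1, and no planned analysis restores the excluded classes.

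**2. The plan's own figures.** Table 4 gives Aim 2 gait-speed power of 90% (140 vs 60) and 78% (60 vs 60). With a two-sample t-test, two-sided alpha 0.05, difference 0.10 m/s, SD of change 0.20 m/s, 10% attrition and the table's factor of 0.90, the effective n is N × 0.9 / 0.90 = N. This gives 89.7% and 77.5%, so the figures reproduce. The point does not rest on an arithmetic error.

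**3. Size of one exclusion.** Section 3 caps a class at 10; Table 4 anticipates 60 per staff-led arm.
- Staff-led arm: 60 / 10 = 6 full classes; one class is 10 / 60 = 17%.
- Pooled On the Move group for Aim 4: 140 + 60 = 200; one class is 10 / 200 = 5%.

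**4. Possible bias (illustration only).** The documents give neither the frequency of mid-course replacements nor event rates by class. Assume six classes of 10, with events in 20% of participants in stopped classes and 5% in the others, and a gait-speed gain 0.05 to 0.10 m/s smaller in stopped classes. With k classes stopped:
- as-randomised event rate = (0.20 × 10k + 0.05 × (60 − 10k)) / 60
- upward shift in the staff-led mean gain after exclusion = (k / 6) × 0.05 to (k / 6) × 0.10

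| Classes stopped | Event rate as randomised | Event rate after exclusion | Shift in mean gait-speed gain |
|---|---|---|---|
| 1 | 7.5% | 5% | 0.008 to 0.017 m/s |
| 2 | 10% | 5% | 0.017 to 0.033 m/s |
| 3 | 12.5% | 5% | 0.025 to 0.050 m/s |

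The target difference is 0.10 m/s. If stopped classes do no worse than the rest, the bias is nil and only information is lost.

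**5. Reverted classes in Aim 1.** From Baseline 1, their change covers about 12 weeks of waiting plus 12 weeks of class, or 24 weeks. From Baseline 2 it covers about 12 weeks, as for first-phase participants. Section 9.3.2 permits either reading. In the three-arm sensitivity analysis the same person could supply a waiting-period change as a control and a class-period change as an active participant, and no rule covers this. Conversely, read literally, the exclusion from all analyses would also discard the wait-list data of a class stopped mid-course, although those data precede the event.

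**The case against.** **The affected aims are exploratory and conditional.** Aim 2 concerns staff who can be trained to lead a class, has no fixed sample size, and includes documenting barriers to finding and training staff. Aim 3(b) sits under the exploratory analyses, so a failed staff class is not hidden altogether. This stands and lowers the severity. It does not justify dropping randomised participants and their events from a comparison that will still be reported.

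**Safety oversight is separate.** Sections 7.5 and 7.8 send events to the IRB, and unblinded staff track imbalance between groups. A reader might infer that adverse events are lost to the trial; they are not. They are lost to the planned comparisons.

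**A switched class has mixed delivery.** Analysed as randomised, it no longer describes pure staff delivery. That is fair, and is why a result without such classes is worth showing as a sensitivity analysis.

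**Reversion does not cross the Aim 1 arms.** Programme is randomised by facility, and a reverted class receives its facility's programme. This is correct: a reader might infer that the programme comparison is broken, and it is not. Including these people is defensible once their baseline is fixed.

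**Unequal or outcome-driven reversion is conjecture.** A reader might expect more reversion in the mostly standing On the Move classes. No document says so, and the readiness criteria in section 3 (attendance at training and at sessions, interaction with participants, understanding of the programme) are not participant outcomes.

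**Loss of Aim 1 power is not supported.** A reader might infer that reverted classes let 280 be reached from fewer, larger facilities. Section 4 anticipates about 34 sites and section 12 at least 28. With intracluster correlation 0.1 and 280 × 0.9 = 252 completers, 28 facilities give 9 each, a design effect of 1 + 8 × 0.1 = 1.80 and gait-speed power of about 84% (normal approximation). With 34 facilities the design effect is about 1.64 and power about 87%. The stated 80% holds at both counts.

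**Conclusion.** The exclusion sentence conflicts with the plan's own intention-to-treat statement and should be fixed. Followed as written, it can bias staff-led efficacy and safety in Aims 2 and 3(b), and can remove harms from Aim 4, at 17% of a staff-led arm per full class. The direction (staff delivery looks better) rests on the assumption that classes stopped for safety do worse. That is plausible because the trigger is a safety judgement, but it is not documented. The size cannot be fixed, because the frequency of such stops is not given and the rates in the illustration are assumed.

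The Aim 1 point is narrower: an unspecified baseline for reverted classes, and possible double use of the same people in the three-arm sensitivity analysis. Neither invalidates the programme comparison. Because the exclusion acts on exploratory aims, this is a change that should be made, not a flaw that undermines the primary result.

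**What to change.** 1. Delete the sentence in 8.2 that excludes mid-course switches from all analyses.
2. In 9.3.3, state that these classes are analysed as randomised (staff-led) in Aims 2 and 3(b), that all their adverse events are retained there and in Aim 4, and that results without them are shown only as a sensitivity analysis.
3. In 9.3.2, state that reverted classes in Aim 1 are measured from Baseline 2, and report the Aim 1 estimate with and without them.
4. For the three-arm sensitivity analysis, state whether reverted participants count as controls, as active participants or as both and, if both, how the repeated contribution is handled.

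The cost is protocol wording and two additional sensitivity results. No new data are needed: section 6.2.3 already assesses all participants after the class, and section 6.2.2 already collects Baseline 2. The rules on who may lead a class, and when a leader is replaced, are unaffected.

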### 8.3 Voluntary Participation

The participants' participation in this research study is completely voluntary. The participant may withdraw, at any time, their consent for participation in this research study. Any identifiable research information recorded for, or resulting from, their participation in this research study prior to the date that they formally withdrew their consent may continue to be used and disclosed by the investigators. To formally withdraw consent for participation in this research study the participant should provide a written and dated notice of this decision to the principal investigator of this research study. If the participant withdraws from the intervention, study staff will ask permission to continue to follow the participant for follow-up assessment. If participation is discontinued for medical reasons and the participant is unable to complete the performance-based testing, all attempts will be made to obtain the self-reported outcomes.

## 9 STATISTICAL CONSIDERATIONS

### 9.1 General Design Issues

A randomized trial is needed to control for confounding factors that affect the outcome. There are no ethical issues regarding a randomized trial since both groups will be receiving an active exercise intervention delivered by trained personnel. We carefully considered the advantages and disadvantages of randomizing at the level of the facility and the resident. Given the amount of interaction that occurs between subjects within a facility, it is imperative that we conduct a cluster randomized trial, and randomize by facility to exercise programs. If we randomize at the resident, participants would discuss details of their intervention and cause cross-contamination between the intervention arms. Unlike a traditional trial in which participants are randomized as they are being recruited, a cluster randomized trial also affords the additional benefit of examining the facility characteristics such as type (independent living/senior high rise) and size, and ensuring a balance in those characteristics is achieved by design rather than chance. Once the facilities are randomized to exercise program, we will then randomize within facility for delivery mode (i.e. subjects will be randomized to either an exercise leader or staff activity person led exercise program). Randomization for delivery mode will occur after baseline testing. We will use a commercially available high quality pseudo-random deviate generator such as that available in SAS® (SAS Institute, Inc., Cary, North Carolina) known to be free of serial correlations(56) to randomize facilities to the two arms in a 1:1 ratio, stratified by facility type. In addition, the proposed design reaps the advantages of a paired comparison for the exploratory hypothesis (Aim 2) as both exercise leaders and staff activity personnel will be delivering On the Move in the same set of facilities, where feasible to train a staff person ready to lead the class safely and per protocol.

The main outcomes are self-reported function and disability (Late Life Function and Disability Index/LLFDI) and walking ability (6-minute walk test/6MWT and gait speed). We will also examine satisfaction, attendance rates and adverse event (falls, soft tissue injuries, muscle soreness, etc) rates.

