### **3 STUDY DESIGN**

To address our research questions, we will conduct a cluster randomized single-blind two arm intervention trial to compare the effects on function, disability and mobility of a standard group exercise program and a novel *On the Move* group exercise program in 400 community-dwelling older adults who reside in independent living facilities and senior housing sites or who attend senior community centers. Group exercise classes are twice weekly for 12 weeks and will be delivered by exercise leaders and activity staff personnel. Function, disability and mobility are assessed at baseline and post intervention (**Figure 1**).

[figure not shown]

Figure 1.

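### Section 9.1 says balance in facility type and size is achieved by design, but the randomisation is stratified by type only, the type levels are not listed, and the Aim 1 primary model contains neither factor

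*Supplement*

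**What the plan says.** All references are to protocol version 2.0.

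Section 9.1 gives as one advantage of cluster randomisation "examining the facility characteristics such as type (independent living/senior high rise) and size", and continues with "ensuring a balance in those characteristics is achieved by design rather than chance". Further down the same paragraph comes the operational rule: a pseudo-random generator will be used "to randomize facilities to the two arms in a 1:1 ratio, stratified by facility type". Size does not appear in that rule.

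Section 3 describes the population as "older adults who reside in independent living facilities and senior housing sites or who attend senior community centers". Section 4 agrees: "We will recruit participants from the UPMC Independent Living Facilities (ILFs), other Independent Living Facilities, Senior Housing sites, and Community Centers". Its site count, however, covers two types only: "We anticipate enrolling subjects from 10 ILFs and from approximately 24 of the Senior Housing sites for a total of approximately 34 sites". The Section 12 timeline likewise mentions only independent living facilities and senior high rises.

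The Aim 1 model in Section 9.3.2 has intervention arm and the baseline value of the outcome as fixed effects, and a random effect for facility. Other baseline measures may be added as a robustness check if they differ significantly between arms or are judged important. Facility type and size are not named there.

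**The concern.** The plan itself picks out two facility characteristics as worth balancing and tells the reader that the design takes care of both. The scheme it then specifies can do so for only one. A reader of the trial report would take comparability of facility size between arms as guaranteed, when it is not.

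The guarantee for type is also incomplete. A stratified list cannot be drawn up, or checked afterwards, until the levels of the factor are written down. The text does not say whether a community center forms its own stratum, is placed with one of the two named types, or is allocated outside the strata.

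Nor does the primary analysis supply what the randomisation leaves out. A facility random effect accounts for correlation among participants at the same site. It does not adjust the arm comparison for a difference between arms in a facility-level characteristic.

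**Working it through.** The plan attaches no figure to this point, so the main check sets the passages side by side.

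1. **Characteristics said to be balanced** (Section 9.1): type and size.
2. **Factors in the allocation rule** (Section 9.1, same paragraph): type.
3. **Other devices that could balance size**: none is described in the protocol.
4. **Result for size**: claimed by design, delivered by chance.
5. **Levels of type**: the stratification sentence lists none. Section 9.1 elsewhere names two. Sections 3 and 4 recruit from a third kind of site. The level for that third kind is undefined.
6. **Adjustment in the primary model** (Section 9.3.2): arm, baseline outcome and facility random effect. Type and size are absent.

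**Illustration of what chance can do to size.** The documents supply 10 independent living facilities and about 24 senior housing sites, allocated 1:1 within type, so 5:5 and 12:12. The following is assumed, not documented: half the sites of each type are large (5 and 12, so 17 in all), each stratum is filled exactly, and there are no community centers.

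The number of large sites in one arm is X = X1 + X2, with
- X1 ~ hypergeometric (10 sites, 5 large, 5 drawn)
- X2 ~ hypergeometric (24 sites, 12 large, 12 drawn)

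The difference between arms is D = X − (17 − X) = 2X − 17. Exact summation gives:

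| Split of 17 large sites | Probability |
|---|---|
| 9 vs 8 | 0.50 |
| 10 vs 7 or worse | 0.50 |
| 11 vs 6 or worse | 0.18 |
| 12 vs 5 or worse | 0.04 |

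With size also stratified, the same example gives 6:6 among large senior housing sites and 3:2 among large independent living facilities, which is 9 vs 8.

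**Effect on arm totals.** Suppose size imbalance did carry over to enrolment. The equivalent equal-arm number is 2·n1·n2/(n1 + n2).
- 160 vs 120: 2 × 160 × 120 / 280 = 137, against 140 planned, a loss of about 2%.
- 150 vs 130: 2 × 150 × 130 / 280 = 139.3, a loss of about 0.5%.

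Both are before clustering. The loss is too small to carry an argument.

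**Cost of adjusting.** With 34 facilities and two arms there are 34 − 2 = 32 between-facility degrees of freedom. Three type levels take 2 and a single size term takes 1, leaving 29. At the 28 facilities that Section 12 gives as a minimum, the count is 28 − 2 − 3 = 23.

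**The case against.** The strongest reply is that the allocation rule is clear and the disputed words are only rationale. They stand in a general case for cluster randomisation, and the mention of size looks like a remnant of version 1, which stratified by type and size. Dropping size is a change between versions and no fault in itself. With sites added until 280 participants are enrolled, fewer strata is a defensible choice. All of that stands. It explains how the mismatch arose, but the current text still asserts a property that its own rule does not deliver.

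The reply also rightly limits four stronger readings that a reader might draw.

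- **That type has exactly two levels, so community centers are certainly unbalanced.** The two types appear in a parenthesis after an expression of example, and the stratification sentence lists no levels. A third stratum may exist in practice. The text supports only that the levels are undefined. Community centers are also missing from the residence criterion in Section 4.1 and from the site count, so the gap here is part of a wider one.
- **That size imbalance biases the result.** Chance imbalance under valid randomisation does not bias the estimate, and the protocol nowhere links facility size to outcome.
- **That arm totals are threatened.** Nothing ties enrolment to facility size, classes are capped at 10, and even a 160 vs 120 split costs about 2%.
- **That the remaining facilities must be re-stratified.** Version 2.0 is dated December 2015 and recruitment was to run to March 2016, so few sites may have been left. Three types by two sizes would make six strata for them.

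Finally, the plan does handle some imbalance. Section 9.3.1 provides for covariate adjustment when participant characteristics differ significantly between arms, and Section 9.3.2 allows further covariates for robustness. These cover differences between residents in part. They name no facility characteristic, and they depend on what the data show, so they do not replace prespecified adjustment.

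**Conclusion.** The point holds as an internal contradiction with a gap in specification. Balance by design is claimed for type and size; the randomisation provides it for type only; the levels of type are not stated; and the primary model includes neither factor. The first of these rests on the wording of a single paragraph and needs no assumption.

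The consequence is modest. The Aim 1 comparison remains valid. What is lost is a protection that the plan tells the reader it has, together with the chance to adjust in the primary analysis for two characteristics that the plan itself singles out. The probabilities of 0.50 and 0.18 show that a visible size difference between arms would be unremarkable with about 34 sites. They depend on the assumed half-large split and say nothing about harm. The same assumptions give an even chance of the closest possible split, 9 vs 8.

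**What to change.** 1. In Section 9.1, limit the statement on balance by design to facility type.
2. List the levels of facility type used in the randomisation, and state where community centers fall. If some centers were allocated without a stratum, say so.
3. In the Aim 1 mixed model of Section 9.3.2, prespecify facility type and facility size as fixed covariates in the primary analysis, before outcomes are compared by arm. Define size so that it exists for every kind of site. A count of residents does not serve for centers that people attend without living there; one option is the number of people aged 65 or older who live at or regularly attend the site. Take the measure before the facility is allocated, and do not use the number enrolled, which could itself respond to allocation.

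The text changes cost nothing. The covariates need one extra item per facility and use about 3 of 32 between-facility degrees of freedom at 34 sites. Adding size to the stratification for any facilities not yet randomised is optional; with few sites left, small or incomplete strata may take away most of the gain.
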